### Intervention

Eligible patients will be asked to provide informed consent to participate in the study. Next, enrolled patients will be randomized to receive either BST or the placebo, which will both be orally administered at a dose of 10 g twice daily for 4 weeks for a total daily dose of 20 g.

#### Banha-sasim-tang (BST)

Each 10 g of the BST syrup prepared by Jeong-woo Pharmaceutical Company Ltd., (Seoul, Korea) will be produced according to Korean Good Manufacturing Practice. BST soft extract is composed of the following herbs: *Pinelliae* tuber (1.178 g), *Scutellariae radix* (0.840 g), *Ginseng radix* (0.803 g), *Glycyrrhizae radix* (0.732 g), *Zingiberis rhizoma* (0.500 g), *Zingiberis rhizoma recens* (0.077 g), *Coptidis rhizoma* (0.133 g), and *Zizyphi fructus* (0.512 g). β-Cyclodextrin (1.500 g), apple concentrate (1.350 g), carboxymethyl cellulose (50 mg), sodium benzoate (5.4 mg), and water will be included as excipients in each 10 g of BST soft extract.

#### Placebo

The placebo, which will be provided by the same supplier (Jeong-woo Pharmaceutical Company Ltd., Seoul, Korea), will contain starch (0.600 g, lactose mixture (1.412 g), caramel food coloring, and excipients and will have a color and taste similar to those of the BST soft extract with no active components. At the end of the study, participants will indicate whether they thought that the drug they were administered was the active drug or the placebo to evaluate the success of blinding.

#### Concomitant medication

Medications that may affect the efficacy of the trial medication, including NSAIDs, corticosteroids, and GI motility-related drugs will be prohibited. Patients will receive treatment for severe symptoms immediately they occur. However, the patients can be excluded under the request for other medications to relieve the symptoms of FD.

### Outcome measures

#### Primary outcome measure

The primary efficacy parameter is the change from baseline in the total score of the Nepean Dyspepsia Index (NDI) symptom-based questionnaire [19]. The NDI was developed to measure the severity of dyspepsia symptoms and is composed of two parts: a symptom-based questionnaire and a quality-of-life (QoL) evaluation. The Korean version of the NDI (NDI-K) symptom-based questionnaire, which was translated into Korean and validated [20], will be used as the primary outcome measure. The NDI-K symptom-based questionnaire scale consists of the questions about the following 15 dyspeptic symptoms: burping/belching; fullness after eating or slow digestion; nausea; inability to finish a regular meal; bad breath; regurgitation of bitter/sour tasting fluid into the mouth or throat; vomiting; and discomfort, cramps, burning sensation, pain or ache, pressure, and bloating in the upper abdomen; as well as a burning sensation (heartburn), and pain in the chest.

Three aspects, consisting of symptom severity and frequency and symptoms experienced out of the 15 items, will be assessed using a 5-point Likert scale: none, 0; slight, 1; moderate, 2; severe, 3; and very severe, 4. The NDI scale is easy for participants to understand and adequately reflects their symptoms. The NDI-K symptom-based questionnaire scale will be assessed at baseline, and week 2 and 4 during oral administration of BST, and at 4 weeks after completion of BST administration.

#### Secondary outcome measures

Outcome measures will consist of the following items:The efficacy parameter is a change from baseline in the total score of the QoL section of the NDI-KThe efficacy parameter is a change from baseline in the total score of the validated FD-related QoL (FD-QoL) scale [21]Assessment of gastric myoelectrical dysrhythmias (GMA)The efficacy parameter is a change from baseline in the total score of the Visual Analog Scale (VAS) for measuring severity or pain

### Safety assessment

The safety assessment, consisting of vital sign measurements, electrocardiography, and liver and renal function tests will be conducted at visits 2 and 4.

### Randomization

In this study, patient randomization will be performed with a group allocation ratio of 1:1. The random sequence will be generated using a computer-generated random number table, and random numbers will be assigned using sealed, opaque envelopes. Both the patients and clinicians will be blinded until the end of the trial. The research team involved in the treatment administration and data collection will not have a role in the assignment process.

### Sample size calculation

The objective of this study is to validate the effect of BST treatment on FD. In this study, the sample size will be estimated based on the results of several clinical experiences and two previous studies [22, 23]. The average variation (*δ*) is assumed to be 20 and the standard deviation (SD = *σ*) is assumed to be 22.4 between the treatment and the placebo (control) groups. In addition, the patients will be allocated at a 1:1 ratio to each group and assessed a two-sided test after considering 5% significance and 80% power levels. Therefore, this study will include 40 participants, who will be divided into two groups of 20 (*n*) each:$$ n=\frac{2\times {\left({Z}_{\alpha /2}+{Z}_{\beta}\right)}^2\times {\sigma}^2}{\delta^2}. $$

Considering a potential dropout rate of 20%, this study will require at least 50 participants.

### Monitoring

The study monitoring will follow Good Clinical Practice principles and will be processed by Korea Institute of Oriental Medicine. A clinical research associate (CRA) will be in attendance every 4 weeks to monitor and ensure the quality of the recorded data. The CRA will check the medical records, informed consent forms, source documents, and the electronic CRFs.

### Evaluation of adverse events (AEs)

AEs are any adverse, unintended changes in vital signs, symptoms, or laboratory tests that occur after patients have participated in the clinical trial. All participants will be requested to report any AEs that occur during the trial, and each AE must be recorded in the CRFs by the investigator. In addition, all AEs will be assessed for causality, and when serious AEs occur, the Institutional Review Board (IRB) and principal investigator will be notified as soon as possible. After receiving a serious AE report, the site investigator will decide whether the participant should be withdrawn from the trial.

### Data collection and analysis

This trial will last for 9 weeks, including 4 weeks of study drug administration and the follow-up period. Participants will attend four assessment visits after screening and complete a set of questionnaires and other evaluations (Table 1). Data will be collected using electronic spreadsheets, which will be completed by practice nurses.

**Table 1 Tab1:**
[figure not shown]
Schedule for enrollment, intervention, and assessment

*BST Banha-sasim-tang*, *ECG* electrocardiogram, *GMA* Gastric myoelectrical dysrhythmias, *FD-QoL* Functional dyspepsia-related quality of life, *NDI-K* Korean version of the Nepean Dyspepsia Index, *QoL* quality of life, *PA* posterior-anterior, *VAS* Visual Analog Scale

Data will be analyzed using the intention-to-treat analysis and will include all participants who will undergo randomization. The analysis will be performed considering each individual as a unit of analysis. All reported *p* values will be two-tailed and for each analysis, *p* < 0.05 will be considered statistically significant. Data will be described as the mean, standard deviation (SD) or frequency, percentage, and confidence interval (CI). Category-type data will be analyzed using the Pearson’s χ^2^ test or Fisher’s exact test. Measurement and rating data will be described using the Student’s *t* test and the Wilcoxon rank sum test, respectively. Missing data will be imputed using multiple imputations and the statistical analysis will be performed using the statistical analysis SAS software (version 9.4, SAS Institute Inc., Cary, NC, USA).

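### The named tests for scores leave baseline NDI-K out of the primary comparison; the test is valid, but adjusting for baseline would generally be more efficient and needs no extra patients

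*Protocol article*

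**What the plan says.** Under Primary outcome measure, the Protocol article states: "The primary efficacy parameter is the change from baseline in the total score of the Nepean Dyspepsia Index (NDI) symptom-based questionnaire". The same section schedules the baseline value that an adjusted analysis needs: "The NDI-K symptom-based questionnaire scale will be assessed at baseline, and week 2 and 4 during oral administration of BST", with a further assessment four weeks after dosing ends.

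Under Data collection and analysis, the methods are sorted by type of data. For scores, "Measurement and rating data will be described using the" Student's t test (measurement data) and the Wilcoxon rank sum test (rating data). The analysis set is everyone randomized: "Data will be analyzed using the intention-to-treat analysis and will include all participants who will undergo randomization". Missing values are to be multiply imputed.

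The Sample size calculation uses the two-sample formula for means without a covariate. The difference "is assumed to be 20 and the standard deviation" "is assumed to be 22.4 between the treatment and the placebo (control) groups", with 20 evaluable per group and 50 enrolled. The article names no ANCOVA, mixed model or baseline covariate.

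**The concern.** A two-sample test on change from baseline fixes the coefficient of the baseline score at 1. When baseline and follow-up variances are equal, the coefficient that minimises the variance is the correlation r between the two visits, which is below 1. The change score therefore over-corrects for baseline. This has two consequences:

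- **Efficiency.** The standard error is larger than it need be, in a trial whose planned size only just meets its 80% target.
- **Chance imbalance.** If one arm happens to start with higher scores, it tends to show a larger fall through regression to the mean, and the unadjusted difference carries part of that imbalance. With about 20 per arm such imbalances are not small. Entry also requires a minimum symptom severity (Inclusion criteria), which makes regression to the mean a realistic concern.

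Baseline NDI-K is already scheduled, so leaving it out of the model saves nothing.

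**Working it through.** **Inputs from the article.** Difference 20; SD 22.4; two-sided 5% significance; 80% power; 1:1 allocation; 20 evaluable per arm; 20% dropout.

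**Assumptions, because the article does not give them.**
- 22.4 is the SD of the change score.
- Baseline and follow-up variances are equal.
- The baseline-to-follow-up correlation r lies between 0.3 and 0.9.

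**1. The plan's own figure.** n = 2 × (1.960 + 0.842)² × 22.4² / 20² = 19.69, so 20 per arm and 40 in total; 40 / 0.8 = 50. Both stated sizes reproduce. Power at 20 per arm is 80.6% by the normal approximation that the plan uses. By the t distribution it is 78.6% (38 df; noncentrality 20 / (22.4 × √(2/20)) = 2.82).

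**2. Variance under adjustment.** With a common visit SD of s, the change score has variance 2s²(1 − r), and the ANCOVA residual has variance s²(1 − r²). The ratio is (1 + r)/2, so the residual SD is 22.4 × √((1 + r)/2).

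**3. Power with 20 per arm.** The ANCOVA figures use 37 df (one lost to the covariate), with the residual SD multiplied by √(1 + 1/36) to allow for chance baseline imbalance. The simulations used 8,000 trials per value of r.

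| r | Variance ratio | Residual SD | ANCOVA power | Simulated: change t test vs ANCOVA |
|---|---|---|---|---|
| 0.3 | 0.65 | 18.06 | 92.0% | 79.8% vs 92.3% |
| 0.5 | 0.75 | 19.40 | 87.9% | 78.2% vs 87.9% |
| 0.7 | 0.85 | 20.65 | 83.7% | 78.3% vs 83.6% |
| 0.9 | 0.95 | 21.83 | 79.5% | 78.8% vs 79.7% |

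Against 78.6% unadjusted, the gain is about 13, 9, 5 and 1 points.

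**4. If 22.4 is the SD of a single-visit score.** The change SD is then 22.4 × √(2(1 − r)) and the ANCOVA SD is 22.4 × √(1 − r²). By the normal approximation, power moves from 66.5% to 84.1% (r = 0.3), from 80.6% to 90.3% (r = 0.5) and from 95.4% to 97.7% (r = 0.7).

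**5. If the variances differ.** Let the follow-up SD be k times the baseline SD. The ratio becomes k²(1 − r²) / (1 + k² − 2rk). At an assumed k = 1.25 it is 1.422/1.813 = 0.78, 1.172/1.313 = 0.89 and 0.797/0.813 = 0.98 at r = 0.3, 0.5 and 0.7. The gain nearly disappears at r = 0.7.

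**6. Effect of chance imbalance.** Under the step 2 assumptions, s = 22.4 / √(2(1 − r)). A baseline difference of one standard error, s × √(2/20), shifts the change-score estimate by (1 − r) times that amount:
- r = 0.3: 0.7 × 5.99 = 4.2 points
- r = 0.5: 0.5 × 7.08 = 3.5 points
- r = 0.7: 0.3 × 9.15 = 2.7 points

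That is 14% to 21% of the assumed effect of 20.

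**The case against.** The strongest reply is that nothing here is an error. In a 1:1 randomized trial, a two-sample test on change holds its type I error and is unbiased over randomizations. It also agrees with the declared endpoint and with the sample-size formula. That stands. A reader might infer that the planned analysis is invalid or biased, but the article does not support it: the bias is conditional on an imbalance that arises by chance and averages to zero.

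A second reply is that a condensed article leaves the model to a statistical analysis plan. This carries less weight, because the article does name the tests. A covariate added later would change the stated method, not fill a gap.

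A third is that the article does not assign a test to the NDI-K total. The tie between the tests and the change score comes from reading two sections together, and a total built from Likert items could be treated as rating data and go to the Wilcoxon test. That is fair. The power figures apply to the t test only, and none were computed for the rank test. Neither test adjusts for baseline, so the point holds whichever is used.

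Finally, the gain rests on an unstated correlation, on equal variances and on the meaning of 22.4. That stands too, and it is why the size is given as a range.

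**Conclusion.** The point holds as one of efficiency and protection against chance imbalance, and it should be acted on. If 22.4 is the SD of change and the variances are equal, adjustment raises power with 20 per arm from 78.6% to about 92%, 88% or 84% at r = 0.3, 0.5 or 0.7. The gain falls to about 1 point at 0.9, and over the 0.3 to 0.7 range it shrinks if scores are more variable at follow-up than at baseline.

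Two stronger readings are not supported. First, a reader might take 78.6% to mean that the trial is wrongly sized. The stated sizes follow correctly from the plan's inputs and formula, and the two-point gap to 80.6% is the difference between the t distribution and the normal approximation. Second, a reader might expect a narrower interval for every score outcome. The article gives no SD or correlation for NDI-K QoL, FD-QoL or VAS, so a similar gain there is likely but is neither guaranteed nor quantified.

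**What to change.** Before unblinding, specify the primary analysis as an ANCOVA of the NDI-K symptom total at the primary time point, for example the end of treatment at week 4, on treatment with baseline NDI-K as covariate. The article lists several assessments without designating one as primary, so the time point should be named in the same edit. Report the adjusted mean difference with its 95% CI, pooled over the multiple imputations.

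Modelling the change instead of the follow-up score gives the same treatment estimate once baseline is in the model, so the declared endpoint can stay. Use the same model for NDI-K QoL, FD-QoL and VAS, each with its own baseline, and keep the unadjusted test as a sensitivity analysis.

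The cost is wording in the protocol and analysis plan. No patients, visits or measurements are added, the sizes of 40 and 50 stay, and the model is standard in the SAS software already named. The timing matters because the article describes the trial as ongoing, and a covariate chosen after unblinding could look data-driven.

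### The primary test is not fixed: the rule splits measurement from rating data without placing the NDI-K change score, while the sample size assumes a comparison of means

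*Protocol article*

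**What the plan says.** Four statements in the protocol article bear on this.

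- **Test rule** (Data collection and analysis, text after Table 1). Continuous and ordinal outcomes are split into two classes, measurement data for Student's t test and rating data for the Wilcoxon rank sum test. The sentence ends, and the missing-data method follows: "test and the Wilcoxon rank sum test, respectively. Missing data will be imputed using multiple imputations". No outcome is assigned to either class. The same paragraph lists the mean, SD and CI among the summaries to be reported.
- **Primary outcome** (Primary outcome measure). It is the change from baseline in the NDI-K symptom total. There are 15 symptoms and three aspects, and these "will be assessed using a 5-point Likert scale: none, 0; slight, 1; moderate, 2; severe, 3; and very severe, 4".
- **Sample size** (Sample size calculation). The difference "is assumed to be 20 and the standard deviation" "is assumed to be 22.4 between the treatment and the placebo (control) groups". The calculation uses the normal-theory formula for two means, "assessed a two-sided test after considering 5% significance and 80% power levels". It concludes that "this study will include 40 participants, who will be divided into two groups of 20", and then: "Considering a potential dropout rate of 20%, this study will require at least 50 participants".
- **Assessment times** (Primary outcome measure). The NDI-K symptom score is taken at baseline as well as afterwards, so a baseline value is available for adjustment.

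**The concern.** The document states a test rule, a powering model and a missing-data method, but it does not connect the rule to the primary outcome. Someone who looks at the Likert items would file the NDI-K total under rating data and run a rank test. Someone who looks at the sample size would file it under measurement data and run a t test. Both could claim to follow the protocol.

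Three things are at stake. First, if the choice is left until the data are seen, the test can be picked by its result. Second, the stated 80% power comes from a formula that matches neither named test exactly, and it matches the rank test less well. Third, both named tests compare the arms without adjusting for baseline. A change score subtracts the baseline but does not adjust for it as a regression would, so precision that costs nothing is left unused.

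**Working it through.** **Inputs.** From Sample size calculation: difference δ = 20, SD σ = 22.4, two-sided α = 0.05, power 80%, 1:1 allocation, 20% dropout.

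**1. The plan's own figure.**
n = 2 × (1.960 + 0.8416)² × 22.4² / 20² = 19.69, so 20 per arm and 40 evaluable. With dropout, 40 / 0.80 = 50. The stated 20, 40 and 50 all reproduce.

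**2. Power at these inputs for each candidate test.** The t-test figures use the noncentral t distribution. The Wilcoxon figures come from 20,000 simulated trials of rounded normal data.

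| Per arm | Normal formula | t test | Wilcoxon (normal data) |
|---|---|---|---|
| 20 | 80.6% | 78.6% | about 76% |
| 25 | 88.4% | 87.1% | about 85% |

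The drop from 80.6% to 78.6% is the gap between the normal formula and the t test, and it arises whichever reading is taken. Only the further 2 to 2.5 points belong to the choice of test.

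**3. The same gap in patients.** The t test needs 20.70, so 21 per arm. For the Wilcoxon test, dividing by its large-sample efficiency for normal data gives 19.69 / 0.955 = 20.6, so 21 per arm, 42 evaluable, and 42 / 0.80 = 52.5, so 53 recruited. At the worst-case efficiency, 19.69 / 0.864 = 22.8, so 23 per arm, 46 evaluable, and 46 / 0.80 = 57.5, so 58 recruited. The efficiencies and the shift model are assumptions, not figures from the protocol.

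**4. What an open choice does.** Simulations at 20 per arm with SD 22.4 used two assumed shapes, normal and skewed (gamma, shape 1.5).
- With no true effect, declaring success when either test gives p < 0.05 raises the error rate from about 5% to roughly 6% to 6.6%.
- At a true difference of 20, the two tests reach different verdicts in about 5.5% of trials with normal data and about 12% with skewed data.
- With the skewed shape the Wilcoxon test has more power than the t test, so the small loss in step 2 is specific to normal data.

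**5. What baseline adjustment can gain.** Suppose 22.4 is the SD of the change score, baseline and follow-up have equal SDs, and their correlation is ρ. ANCOVA then has residual variance (1 − ρ²)σ₀² against 2(1 − ρ)σ₀² for the change score, where σ₀ is the SD at one visit. The ratio is (1 + ρ)/2. The protocol gives no ρ, so a range is shown.

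| ρ (assumed) | Variance ratio | n per arm by the plan's formula |
|---|---|---|
| 0.3 | 0.65 | 19.69 × 0.65 = 12.8, so 13 |
| 0.5 | 0.75 | 19.69 × 0.75 = 14.8, so 15 |
| 0.7 | 0.85 | 19.69 × 0.85 = 16.7, so 17 |

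Under these assumptions the gain from adjustment outweighs the 2-point difference between the two named tests.

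**The case against.** The strongest reply is that the document already points to a comparison of means. The outcome is a change in a summed score over many items, which is routinely treated as continuous. The trial is sized on a mean difference, and means, SDs and CIs are to be reported. On that reading the t test is the primary test and matches the sample size. This has force. It shows that the mean-based reading is reasonable, but the rule still does not say so. Most of the other efficacy outcomes are also questionnaire or rating scores. If their totals all count as measurement data, the rank-test half of the rule has almost nothing left to govern.

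A reader might go further and infer that the rule assigns the primary outcome to the Wilcoxon test. The document does not support that. It is one reading of an unassigned rule, and other parts of the text weigh against it.

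A reader might also infer that a rank test leaves nothing to combine after multiple imputation. That is too strong. A rank-sum p value alone cannot be pooled by Rubin's rules, but a Hodges-Lehmann shift with its standard error, or a normalised rank statistic, can be. The pooling method is also a detail that an article may leave to the full protocol or SAP.

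It can fairly be added that the power effect is small, and that at least 50 are to be recruited. At 25 per arm with complete data, both tests exceed 80%. Finally, a single sentence naming either test would remove the ambiguity, so ANCOVA is not the only possible remedy. It is preferred because it matches the mean-based sample size and uses a baseline score already collected.

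**Conclusion.** The point holds as a lack of definition. The class of the NDI-K change score is not stated, two tests are admissible, and one natural reading does not fit the sample size. It does not hold as a claim that the plan prescribes the wrong test or an unworkable missing-data method.

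The numerical effect is modest. At 20 evaluable per arm, power is about 78.6% for the t test and about 76% for the Wilcoxon test, against the stated 80% from the normal formula. Neither named test quite reaches the stated figure. These values rest on the protocol's δ and σ and, for the Wilcoxon test, on normal data. The more important effect is that the conclusion could depend on an unfixed choice. On the assumed shapes, the two tests disagree in about 5.5% to 12% of trials at the planned difference. This should be corrected, but it does not threaten the design.

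**What to change.** Before unblinding, state one primary analysis: ANCOVA of the NDI-K symptom total with treatment as the factor and the baseline total as covariate. Report the adjusted mean difference with its 95% CI, pooled over the multiple imputations by Rubin's rules. Keep the Wilcoxon rank sum test as a sensitivity analysis only. Where the data-type rule is kept for other outcomes, say which outcomes fall in each class.

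Restate the power for the analysis used. Without a stated correlation between baseline and follow-up, the t-test figure of about 78.6% at 20 evaluable per arm can be quoted as a conservative value, provided that 22.4 is confirmed as the SD of the change score.

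The cost is wording in the protocol and SAP. No new data, visits or patients are needed. The article reports the trial as ongoing, with patients and clinicians blinded until its end, so the choice can be documented before any comparison by arm is seen.
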